### Patient Examination by Study-Provided Physician (Stage 3)

After laboratory and diagnostic procedures, the patient will proceed to a consultation with a study-provided physician. This physician will, as in Stage 2, complete a structured consultation form through a tablet-based eCRF. The results of this consultation will amend the one from stage 2 in the gold standard panel. Adding a study physician not involved in the patient’s care to confirm the patient’s diagnosis ensures a higher degree of objectivity in the generation of the gold standard. The study physician will be able to refer to the usual HCP’s notes from stage 2, although this will be only allowed at the end of the consultation in order to minimize bias and ensure patient safety.

Although the interaction time between health care staff and the patient in the investigation will be about three times as long as the standard hospital process, this extra time will be compensated for by the study participants being moved forward in the waiting-room queue for examination, clinical testing, and receiving test results (when relevant). The overall effect is that the study participants will have a longer period of interaction at the clinic (with study trackers and study physicians), but will have a similar total visit length at the clinic (ie, less passive waiting time in the waiting room).

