### Patient Examination by Usual HCP (Stage 2)

Having finished step 1, the patients will continue on to a consultation with a usual HCP. In this step, the patient’s diagnosis and a further diagnostic plan for them will be determined as a part of usual care. The usual HCPs will be COs, AMOs, or medical doctors. The usual HCPs in stage 2 will not be the same HCPs that performed the interview in stage 1. During the consultation, the usual HCPs will fill out a standardized electronic form and a structured consultation report form through a tablet-based electronic case report form (eCRF). Afterwards, they will complete the standard hospital forms, record vital signs, and request laboratory or diagnostic procedures as part of usual care.

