The matching of conditions by the physician panel in step 5 will involve matching the diagnoses made by the usual HCP and study-provided physician with the diagnoses made by the reviewer physicians on the physician panel. The same procedure for the DDSS condition list will be carried out by the reviewer physicians. As in step 4, a third reviewer physician will make a final decision if there is disagreement between the 2 reviewer physicians. The primary comparator of the Ada assessment is the differential diagnosis obtained before the addition of vital sign measurement, physical examination, and additional diagnostic tests. Looking at the differential diagnosis list at each point in the patient’s clinical journey is still a relevant point of comparison.

Finally, the data collection performed in these 5 steps will be analyzed (details are in the “Data Analysis” section). In order to determine the usability, usefulness, and acceptability of the prototype DDSS, the usual HCP questionnaires, in addition to the patient questionnaires, will be analyzed and described using methods appropriate to modified Likert-scale questionnaire data [26].

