### Data Analysis

Applying the definition from Gilbert et al [31], we will assess the accuracy and comprehensiveness of the top-1, top-3, and top-5 suggested conditions by the prototype DDSS in comparison to the gold standard differential diagnoses. Data analysis will also be carried out as presented by Gilbert. In short, descriptive tests and statistics appropriate for categorical data will be utilized to compare condition suggestion accuracy. To analyze if the proportion of correct condition suggestions from the prototype DDSS, from the usual HCPs, and from the study-provided physicians are drawn from the same distributions, the chi-squared test will be applied. If there is a significant difference, we will apply a 2-sided post hoc pairwise Fisher exact test to compare the prototype DDSS and the practitioners. Due to the low sample size of this pilot study, it may be the case that the chi-squared tests will not produce significant results. As the study goal is the comparison of the prototype DDSS to usual care, the ratings of the usual HCPs will be strictly anonymized.

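### The three-group accuracy test sets the study physician's post-test diagnosis beside DDSS and usual-HCP lists made before vital signs and tests, so the omnibus test and the study-physician contrasts mix skill with access to results

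*Protocol article*

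**What the plan says.** Four sections of the protocol article bear on this point.

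- **Stage 2, usual HCP.** "During the consultation, the usual HCPs will fill out a standardized electronic form and a structured consultation report form". Vital signs and tests come later: "Afterwards, they will complete the standard hospital forms, record vital signs, and request laboratory or diagnostic procedures as part of usual care". The DDSS list was already produced in stage 1, before this consultation.
- **Stage 3, study physician.** "After laboratory and diagnostic procedures, the patient will proceed to a consultation with a study-provided physician". The physician is to "complete a structured consultation form through a tablet-based eCRF". The usual HCP's notes may also be read, "although this will be only allowed at the end of the consultation in order to minimize bias and ensure patient safety".
- **Measurement Methods (text after Figure 4).** "The primary comparator of the Ada assessment is the differential diagnosis obtained before the addition of vital sign measurement, physical examination, and additional diagnostic tests". It adds: "Looking at the differential diagnosis list at each point in the patient’s clinical journey is still a relevant point of comparison".
- **Data Analysis.** A chi-squared test asks whether the proportions of correct suggestions "from the prototype DDSS, from the usual HCPs, and from the study-provided physicians are drawn from the same distributions". If it is significant, two-sided Fisher exact tests compare the DDSS with the practitioners. Nothing there restricts the study physician's entry to pre-test information.

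The protocol describes two information states elsewhere. The panel reviewers give a list from history and symptoms and then a list from the full file, and the arm 1 study HCP submits a preliminary list that cannot be changed. No such split is described for the study physician.

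**The concern.** A three-group test of diagnostic accuracy can be read as a comparison of diagnostic ability only if the groups had comparable information. Here two sources precede vital signs and tests, and the third follows the tests and can draw on a colleague's notes. A difference between the study physician and either of the others could therefore come from skill, from the results, or from both, and the analysis cannot separate them.

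Two things are at stake. First, the DDSS versus study-physician contrast would be reported as a difference in accuracy when part or all of it may be timing. Second, the omnibus test is the gate for all the pairwise tests. If the study physician's position drives that test, the gate no longer shows that sources on equal footing differ, yet it still releases the DDSS versus usual-HCP test. The pilot is also meant to supply power calculations for a later trial, so a contrast distorted in this way could carry forward.

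**Working it through.** **1. Information available to each source, as described**

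| Source | When recorded | Vital signs and tests available? | Colleague's notes? |
|---|---|---|---|
| DDSS | Stage 1 | No | No |
| Usual HCP | During the stage 2 consultation | No; examination findings possible | Not described |
| Study physician | Stage 3, after laboratory and diagnostic procedures | Yes, by implication | Yes, at the end |
| Stated primary comparator | Before vital signs, examination and tests | No | Not applicable |

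The stage 3 section speaks of procedures rather than results. That results are in hand is implied by the sequence and by the same section's reference to participants receiving test results sooner. The study physician's row does not match the stated comparator. The usual HCP's row matches it on vital signs and tests but perhaps not on examination.

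**2. Does the protocol give a figure to reproduce?** No. It states no accuracy rate, alpha or power, and the minimum of 50 participants is described as pragmatic. Everything below is illustration. The accuracies, the gain and alpha = 0.05 are assumptions.

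**3. Hand calculation.** Take 50 patients, three equally skilled sources, 60% correct before results and 80% after. The counts correct are 30, 30 and 40.

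- Expected correct per group: 100/3 = 33.33. Expected incorrect: 50/3 = 16.67.
- Squared deviations: 11.11 + 11.11 + 44.44 = 66.67.
- Chi-squared = 66.67/33.33 + 66.67/16.67 = 2.0 + 4.0 = 6.0 on 2 df; p = exp(-3) = 0.0498.
- Fisher exact, DDSS versus study physician (30 versus 40 of 50): p = 0.049.

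This example sits on the threshold. With 39 instead of 40 correct, the chi-squared p is 0.090; with 38 it is 0.15. It shows the mechanism and should not be read as a prediction.

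**4. Simulation over a range.** 20,000 runs per setting; 50 lists per source; equal pre-test accuracy of 50%, 60% or 70%; within-patient latent correlation 0 or 0.5; the study physician's accuracy raised by a fixed gain from results only.

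| Gain (points) | Chi-squared rejects | Chi-squared rejects and Fisher DDSS vs study physician significant |
|---|---|---|
| 0 | about 1% to 5% | about 0.5% to 2% |
| 10 | 9% to 19% | 6% to 12% |
| 20 | 53% to 73% | 41% to 62% |
| 25 | 78% to 97% | 65% to 92% |

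A standard two-proportion power calculation for DDSS versus study physician gives 17% to 21%, 53% to 71% and 74% to 92% for gains of 10, 20 and 25 points, which is consistent.

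**5. Direction.** These settings assume that results bring the study physician closer to the reference, which is plausible if the reference is the panel's full-file list. Against the panel's history-only list, a diagnosis revised by test results could agree less often, and the gap could shrink or reverse. Data Analysis does not say which panel list is the reference for this test.

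**The case against.** The strongest reply has five parts.

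- **A single list is inferred from silence.** The article describes one form. The form itself and the data flowchart are not visible, and the remark about looking at the list at each point of the journey is consistent with repeated capture. This stands. A reader might infer that no pre-result study-physician list exists, or that no post-result usual-HCP diagnosis exists; the article establishes neither. What remains is that the stage 3 consultation is placed after the procedures and the analysis does not say which information state it uses.
- **The main comparison is unaffected.** The first primary endpoint and the stated study goal concern the DDSS and usual care, and no primary endpoint names the study physician. This also stands. A reader might infer that the DDSS versus usual-HCP contrast is biased by this timing. It is not, since both lists precede vital signs and tests. The effect on that pair is limited to the gate.
- **The late consultation is deliberate.** It serves the gold standard, and the notes are held back until the end. That justifies the timing for the reference diagnosis, but the same physician is also a tested group. Holding back the notes does nothing about test results.
- **The illustration is assumed, sits on the threshold and runs in one direction.** Agreed. The range of settings and the dependence on the reference list are given for that reason.
- **This is an unpowered pilot that warns of non-significant tests.** This softens the consequence, but a confounded contrast remains confounded at any sample size.

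**Conclusion.** The point holds in a limited form. As the article describes the schedule, the omnibus chi-squared test and the contrasts involving the study physician combine diagnostic skill with access to test results and, at the end of the consultation, a colleague's notes. This conflicts with the pre-test comparator set in Measurement Methods. The DDSS versus usual-HCP contrast is not confounded by this timing, although its pairwise test can be released by an omnibus result that the study physician drives.

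The documents do not allow the gap to be sized. Under the assumed accuracies, a gain of 10 points from results matters modestly, and one of 20 points or more makes a significant omnibus test more likely than not at equal skill. The sign depends on the reference list, so the protocol does not support a reading that the study physician must come out ahead. The verdict also rests on there being no locked pre-result list in the unseen form. If one exists and is the one analysed, the remaining point is that Data Analysis should say so.

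**What to change.** Choose one of two routes, and name the reference list in Data Analysis either way.

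- **(a) Capture a pre-result list.** In stage 3, have the study physician enter and lock a history-based list before opening test results or the usual HCP's notes, then enter a second list after results. Use only the locked list in the three-group test, judged against the panel's history-only list. Cost: one extra locked form page per patient.
- **(b) If that list is not captured**, which may be the case for patients already enrolled, test the DDSS against the usual HCP directly, without the three-group gate. Report the study physician's post-result accuracy descriptively against the panel's full-file list. Cost: one fewer formal comparison.

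Neither route fully equalises information. The usual HCP completes the form during a consultation that may include physical examination, so the report should state that the usual HCP's list may reflect examination findings that the DDSS list and a history-based study-physician list do not.

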### Measurement Methods

Overall, there will be 5 stages in the process of data collection and physician panel assessment (Figure 4 shows an overview). The first 3 stages in this process have already been described: (1) the study HCP will use the prototype DDSS; (2) the patient will consult with a usual HCP; and (3) the patient will consult with the study-provided physician. There are then 2 additional steps: (4) generation of a differential diagnosis by the physician panel, and (5) matching of conditions by the physician panel.

**Figure 4 figure4:**
[figure not shown]
Data flowchart. DDL: differential diagnosis list; DDSS: diagnostic decision support system.

The physician panel in step 4 that makes the differential diagnoses will be made up of 3 local physicians, each with at least 3 years of full-time clinical experience (the majority in general medicine), who will carry out a review process; this process will yield the gold standard differential diagnosis list for each case. The physician panel members have been thoroughly screened and chosen by the principal investigator of this study, who is a native Tanzanian doctor with over 20 years of experience as a medical doctor and several additional years of experience as an instructor at Muhimbili University of Health and Allied Sciences. All physician panelists are required to have an active medical license and to be available for at least 9 hours per week during the physician panel process in order to be immersed enough in the process. Two independent “reviewer” physicians on the panel will review the diagnoses from the usual HCP and the study-provided physician, the pseudo-anonymized medical history, and the symptoms of each patient. They will assign a preliminary differential diagnosis list and a principal diagnosis to each case based on history and symptoms alone and then assign a final differential diagnosis list and principal diagnosis based on the full patient clinical file (this will include vital signs and results from medical examinations and diagnostic tests). In case of disagreement between the 2 differential diagnosis lists, a third reviewer will make a final decision. The tenth revision of the International Statistical Classification of Diseases and Related Health Problems will be used to determine all diagnoses.

The matching of conditions by the physician panel in step 5 will involve matching the diagnoses made by the usual HCP and study-provided physician with the diagnoses made by the reviewer physicians on the physician panel. The same procedure for the DDSS condition list will be carried out by the reviewer physicians. As in step 4, a third reviewer physician will make a final decision if there is disagreement between the 2 reviewer physicians. The primary comparator of the Ada assessment is the differential diagnosis obtained before the addition of vital sign measurement, physical examination, and additional diagnostic tests. Looking at the differential diagnosis list at each point in the patient’s clinical journey is still a relevant point of comparison.

Finally, the data collection performed in these 5 steps will be analyzed (details are in the “Data Analysis” section). In order to determine the usability, usefulness, and acceptability of the prototype DDSS, the usual HCP questionnaires, in addition to the patient questionnaires, will be analyzed and described using methods appropriate to modified Likert-scale questionnaire data [26].

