### Strengths and Limitations of the Current Study

There are several strengths and limitations to this study. It is prospective, unlike previous assessments of DDSS performance, which have mostly been retrospective [10]. The Tanzanian outpatient clinic setting will provide a heterogeneous patient population. Through the application of broad inclusion criteria, we aim to include a diverse patient population with varied conditions covering a wide range of age groups. Another strength of this design is the approach to determining the gold standard diagnosis, which is based on the methods in Gilbert et al [31] and Semigran et al [43] and will use a physician panel and voting methods to achieve high objectivity and independence.

This is a single-site study in the outpatient clinic of a Tanzanian district hospital; therefore, the study’s findings may not be applicable to other LMICs. The relatively small enrollment target of a minimum of 50 participants is another limitation, but as this is a pilot study, this sample size is adequate to enable the design of a definitive later study. The study questionnaires filled out by the participants and the usual HCPs are not based on previously validated instruments and thus response bias cannot be excluded.

Considering the pilot character of this study, the limitations are appropriate, as the findings of this study can be used in the conception of a larger trial that will validate the accuracy and usefulness of a chatbot-based DDSS.

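### The panel sees the usual HCP's and study physician's diagnoses when it sets the gold standard, then scores those diagnoses against it, so the comparison with the DDSS is expected to favour the practitioners

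*Protocol article*

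**What the plan says.** The protocol article describes a five-step process under Measurement Methods.

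- **Step 4, building the reference.** Two reviewers "will review the diagnoses from the usual HCP and the study-provided physician, the pseudo-anonymized medical history, and the symptoms of each patient", and "this process will yield the gold standard differential diagnosis list for each case". They first assign a preliminary list and principal diagnosis, said to rest only on history and symptoms. They then assign a final list from the complete clinical record, including vital signs, examinations and tests. A third reviewer settles disagreements.
- **Stage 3 as an input.** The section on the study-provided physician says of that visit: "The results of this consultation will amend the one from stage 2 in the gold standard panel". On timing it says: "After laboratory and diagnostic procedures, the patient will proceed to a consultation with a study-provided physician". It adds that "The study physician will be able to refer to the usual HCP’s notes from stage 2", but only at the end of the consultation.
- **Step 5, scoring.** Matching involves "matching the diagnoses made by the usual HCP and study-provided physician with the diagnoses made by the reviewer physicians on the physician panel". For the tool, "The same procedure for the DDSS condition list will be carried out by the reviewer physicians". This section also names, as the primary comparator for the tool, the differential that precedes vital signs, examination and tests.
- **Use of the scores.** Under Primary Endpoints, DDSS accuracy against the panel is reported in the context of usual-HCP accuracy. Under Data Analysis, a chi-squared test compares the proportions correct for the DDSS, the usual HCPs and the study physicians. If it is significant, pairwise Fisher exact tests follow.
- **What is claimed.** Strengths and Limitations credits the gold standard with a physician panel and "voting methods to achieve high objectivity and independence".

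**The concern.** The usual HCP and the study physician each have two roles: they supply evidence to the panel, and they are then graded by what the panel concludes. A reviewer who has read a colleague's diagnosis is more likely to list it. Agreement between practitioner and panel therefore no longer measures accuracy alone.

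An expert panel may legitimately draw on treating clinicians' opinions. The difficulty arises when those opinions are also index results in an accuracy comparison, and when another competitor in that comparison, here the DDSS, is not named as having the same access.

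At stake is the benchmark for the first primary endpoint, since Data Analysis describes comparison of the tool with usual care as the study goal. The pilot is also meant to support power calculations for a later trial (Outcomes and Outcome Measures), so a distorted gap could carry forward into that trial's sample size.

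**Working it through.** The protocol gives no figure to reproduce. The sample size (minimum 50) is pragmatic, and no effect size is stated. The check is therefore a reading of the text, followed by an illustration of direction.

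**1. Which sources enter the reference, and which are scored against it**

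| Source | Stated input to step 4? | Scored in step 5? | In the chi-squared/Fisher comparison? |
|---|---|---|---|
| Usual HCP diagnoses | Yes | Yes | Yes |
| Study physician diagnoses | Yes | Yes | Yes |
| DDSS list | Not named | Yes | Yes |

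Two of the three sources compared are stated inputs to the reference. The third is not.

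**2. Which panel list is affected**

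- *Final list.* It is based on the complete record, by reviewers who are said to review both practitioners' diagnoses. It is affected as written.
- *Preliminary list.* The sentence introducing it restricts it to history and symptoms. The sentence just before says the reviewers also review the diagnoses. The stated contrast between the two lists is vital signs, examinations and tests; the diagnoses are not mentioned as held back. The study physician sees the patient after laboratory procedures. If that diagnosis is open at this point, it can carry test information into a list meant to exclude it.

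**3. Which analyses are affected**

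The first primary endpoint (where usual-HCP accuracy is the context) and the tests in Data Analysis use practitioner scores. The second endpoint compares study-HCP lists between arms, and the third compares preliminary with final study-HCP lists within arm 1. Study-HCP lists are not stated step 4 inputs, so this mechanism does not reach those two endpoints.

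**4. Illustration of size (all values assumed)**

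Let p be the practitioner's accuracy against a panel that has not seen the diagnoses. Let a be the share of otherwise non-matching cases in which the panel adopts the diagnosis it was shown. Then

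apparent practitioner accuracy = p + a(1 − p), and the inflation is a(1 − p).

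| p | a = 10% | a = 20% | a = 40% |
|---|---|---|---|
| 50% | 55% (+5) | 60% (+10) | 70% (+20) |
| 70% | 73% (+3) | 76% (+6) | 82% (+12) |

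**5. Effect on the gap to the DDSS (all values assumed)**

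Suppose the DDSS has the same true accuracy p, an adopted diagnosis replaces the panel's own, and m is the chance that the DDSS lists the adopted diagnosis. Then

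apparent DDSS accuracy = p[1 − a(1 − p)] + m·a(1 − p),

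and the spurious gap = a(1 − p)(1 + p − m).

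With p = 60% and a = 20%, a(1 − p) = 0.08. The practitioner scores 0.60 + 0.08 = 68%. The DDSS scores 0.60 × 0.92 = 55.2% with m = 0, or 55.2% + 0.3 × 8% = 57.6% with m = 0.3. The gap is 12.8 or 10.4 points although true accuracy is equal. Since m cannot exceed 1, the factor 1 + p − m is positive, so in this model the gap always favours the practitioner. With a = 0, as when the panel does not see the diagnoses, the gap is 0 for every p and m.

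**The case against.** **The preliminary list may be clean.** Taken literally, a list resting only on history and symptoms excludes the practitioners' diagnoses as well as the tests. If the primary comparator in Measurement Methods means this list, the main comparison could escape the problem. This stands as a possibility. A reader might infer that every panel list is certainly contaminated; the text does not establish that for the preliminary list. Nor does it say that the diagnoses are withheld, and the order of the sentences points the other way. Figure 4 may show the sequence, but its image was not available for this check.

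**Non-display of the DDSS list is inferred.** No sentence says that the panel is kept from it. This also stands. The direction of the bias rests on the list's absence from the stated inputs.

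**Recognition at matching.** A reader might infer that the reviewers know whose diagnosis is whose when they match. The documents do not say that diagnoses carry source labels, and the details of masking may sit in the full protocol. The article calls the matching panel unbiased and says the usual HCPs' ratings are anonymized, but neither statement describes masking the source of each list.

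**Access to the usual HCP's notes.** The study physician may open them only at the end of the consultation, expressly to limit bias. That safeguard narrows the dependence between the two practitioners. It does not alter the fact that both sets of diagnoses go to the panel.

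**It is a pilot, and the bias works against the sponsor's tool.** The protocol says it is not powered to settle its hypotheses and warns that the tests may not reach significance. On the expected direction, this bias would not create a false advantage for the DDSS over practitioners. Both points lower the urgency. They do not make the benchmark sound or the claim of independence correct.

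**Conclusion.** The point holds for the DDSS-versus-practitioner comparison. The practitioners' diagnoses are a stated input to the reference and are then scored against it, which conflicts with the independence claimed in Strengths and Limitations. The final panel list is affected as written. For the preliminary list the text is ambiguous and leans towards being affected.

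The expected direction, in favour of the practitioners, assumes that the panel does not see the DDSS list in step 4. The size is unknown because the protocol gives no basis for an adoption rate. The 5 to 20 points at p = 50% and a = 10% to 40% show what modest to substantial adoption would do; they are not an estimate.

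A reader might extend the point to all three primary endpoints. The documents do not support that: the second and third compare study-HCP lists with one another, and those lists are not stated inputs to the panel.

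**What to change.** - **Step 4.** Give the reviewers the history, symptoms, examination and test results, with the tests held back for the preliminary list as now planned. Withhold the usual HCP's and study physician's diagnosis fields until both the preliminary and the final panel lists are locked. State this explicitly for the preliminary list.
- **Step 5.** Score all sources against the locked lists, presented in one common format with the source masked.
- **If the panel must see the diagnoses.** Report practitioner accuracy descriptively as a component of the reference, take the study physician out of the accuracy test, and correct the objectivity and independence wording in Strengths and Limitations.

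**Cost.** The case packet and the order of locking change. No extra staff are needed. Matching takes place after recruitment and data recording are complete, so patient contact is not altered. The downside is that the panel works without the clinicians' summary opinion.
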